#### Primary outcome measures

##### Health Behavior Inventory

The Health Behavior Inventory (HBI) is a 20-item questionnaire that assesses PCS on a four-point scale, ranging from “never” to “often”, and yields total scores in cognitive and somatic domains. The scale includes youth-report and parent-report versions with established reliability and validity in youth with sports injury [68].

##### Patient Health Questionnaire

We will use the nine-item Patient Health Questionnaire (PHQ-9) to measure severity of depressive symptoms. Reliability and validity of the PHQ-9 have been established in pediatric populations [69]. Parental self-report of depressive symptoms will also be measured using the PHQ-9.

##### Anxiety measures

We will use the Generalized Anxiety Disorder-7 item scale [70] and the 15 anxiety items of the Revised Child Anxiety and Depression Scale [71] for adolescent report on anxiety and parent report on adolescent anxiety.

#### Secondary outcome measures

##### Pediatric Quality of Life Inventory

The Pediatric Quality of Life Inventory (PedsQL) is a 23-item questionnaire that assesses physical, emotional, social and school functioning. The scale includes youth-report and parent-report versions [72, 73].

##### School performance

Parents will complete the eight-item Concussion Learning Assessement and School Survey to measure post-injury academic experiences, including number of days missed, concerns about school performance, impact on grades, and whether the school provides academic support to kids with concussion [74]. This will be repeated at each of the follow-up assessments. Participants’ 1 year pre- and post-injury school attendance and grades will also be obtained from school records as a measure of academic outcomes [31] and will be re-coded using a standardized four point grade-point average (GPA).

#### Other outcome measures

##### Client Satisfaction Questionnaire

The eight-item Client Satisfaction Questionnaire will be used at 6 months to measure adolescent and parent satisfaction with services; it has excellent correlation with changes in symptom score [75]. An open-ended question was added to the end of the client satisfaction questionnaire, “*Please let us know if you have any other thoughts or additional comments about your experience with the care you received during the study*,” to allow participants to share their experiences of the intervention or of the usual care received.

##### Adolescent Sleep Wake Scale (ASWS)

The ten-item version of the Adolescent Sleep Wake Scale (ASWS), including domains of falling asleep, reinitiating sleep, and returning to wakefulness, will be used as a measure of sleep quality [76].

##### TBI-QOL–Headache Pain

TBI-QOL-Headache Pain is a 13-item tool that asks participants to estimate how often they experience different issues associated with headaches and headache pain using a Likert scale [77, 78].

#### Health service and medication utilization

The Zatzick et al. [25] and MacKenzie et al. [79] Parent report will be used to assess adolescents’ pre- and post-sports injury health service utilization. Parents will report on emergency department and outpatient pediatric and any specialty sports medicine care. Parents will also report on types of medication used by adolescents. This will be supplemented by information from the medical record.

#### Moderators of treatment outcome

##### History of sports concussion

Adolescents and parents will provide a retrospective report of previous concussion events or concussion-like symptoms they experience. This assessment will include time of previous concussion events, mechanism of injury, and resulting onset and duration of symptoms. An additional set of questions regarding re-injury during the study time period will be asked in the 12-month survey.

##### Exposure to life stress

For adolescent subjects we will use the UCLA Reaction Index Trauma History to collect information at baseline [80]. This measure asks whether or not the respondent has ever experienced ten specific and different traumatic events. The Life Events Checklist will be collected at the 6- and 12-month time points, asking the respondent about whether or not specific life events occurred in the past 6 months, if the event was good or bad, and the level of effect the event had on the respondent’s life. For parent participants we will use an adapted version of the questionnaire used in the National Comorbidity Study–Trauma History at baseline [81]. This will ask about prior abuse, assault, witnessing or experiencing an accident, disaster, life threating illness, death of loved ones. At 6- and 12-month time points we will use the Stressful Life Events Scale, which asks whether or not a parent has experienced specific events [82].

### Data analysis

#### Data analysis plan and statistical procedures

Descriptive statistics for demographic variables, symptom levels, and functional status will be tabulated by the project statistician. All scales will be scored and subscales described. This process will include examining the data for missing values, appropriate ranges and outliers, as well as construction of consort flow diagrams. All primary statistical analyses will be conducted with the intent-to-treat sample.

The primary purpose of the statistical analyses is to examine and compare trends in quality of life and post-concussive, anxiety, and depressive symptoms longitudinally between adolescents in the intervention and control conditions. The effect of major interest will be the time-by-treatment group interaction term. We hypothesize that intervention adolescents will demonstrate greater improvement than controls in both self-report and parent report of post-concussive, anxiety, and depressive symptomatic and quality of life outcomes over the course of the year of trial participation.

We will use mixed random effects generalized regression models to test this hypothesis for continuous and discrete outcomes [83–86]. These models permit the inclusion of subjects with missing data and allow for individual varying slopes and intercepts over time. In addition, these models will allow use of covariates to model potential sources of non-response bias and time-dependent covariates. This model also allows the specification of random or fixed effects and the form of the serial correlation over time (if heterogeneity changes over time). Prior to these analyses, we will examine baseline group differences using the appropriate statistics for the distribution of the variable. Although randomization should ensure balance between the two groups, it is essential to control for known confounders in the design and analysis to prevent a biased assessment of the treatment effect.

Baseline injury, demographic, or clinical variables found to be statistically significant in this analysis will also be included as covariates in the regression models. Some attrition is expected in the study samples. In prior randomized trials of injured adolescents, the investigative group has achieved 6–12-month follow-up completion rates ≥ 90% [31]. Estimates derived from these rates are incorporated into descriptions of subject flow and power analyses. Assumptions about the nature of missing data are crucial to the type of statistical analysis chosen [87–89]. Full information maximum likelihood estimates from mixed random effects generalized linear models adjust for data missing at random (MAR) [90].

We will use statistical logistic models to determine which, if any, demographic or clinical characteristics, including treatment group membership, are predictive of subject attrition. Any factors observed to explain trends in missing data would be used as covariates in subsequent analyses. In past studies, no sources of consistent variation to explain missing data were found. Based on our low attrition rates and the lack of consistent variation in past investigations, we believe that MAR is a reasonable assumption. However, we will perform a sensitivity analysis using non-MAR techniques. The analysis of missing data is an area of ongoing development, and the investigative group will incorporate the most contemporary approaches in the final analyses [88, 89].

We will test for changes in the GPA at 12 months compared to pre-injury in the intervention group participants compared to those in the control group. We will also examine differences in the scores on standardized tests in the same fashion, as well as examine for differences in time lost from school, including missing whole days as well as missing partial days. Secondary analyses will explore the associations with gender, type of sports injury, pre-injury history of psychiatric disorder or visits, and cumulative lifetime trauma history and any observed treatment effects.

We will examine heterogeneity of treatment effects in the primary and secondary outcomes by examining the interaction of the treatment effect with group membership in distinct subgroups of the population. These will be exploratory analyses. Based on our clinical experience, we hypothesize at least three groups of patients: (1) children with mild PCS who, while the symptoms last longer than for most children, nevertheless do resolve relatively quickly; (2) a group of children with persistent PCS and prior history of substantial psycho-emotional distress; (3) a group of children who have symptoms that affect their quality of life, but which wax and wane over time. We will explore defining these groups (1) a priori using clinical indicators and symptoms and (2) empirically using the study sample data, such as latent profile analysis or trajectory analysis. The analysis will define these groups and examine the heterogeneous effect of the intervention of the recovery profiles of these groups.

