### Objectives and hypothesis

This study was designed to assess whether adolescents with persistent symptoms after sports-related concussion will demonstrate better outcomes when receiving a collaborative care intervention compared to usual care (control) condition. Four main aims are addressed; first, we want to compare the groups with respect to post-concussive, anxiety, and depressive symptoms at 3, 6, and 12 months follow-up. Second, we seek to examine the effectiveness of the intervention in improving function and health-related quality of life among adolescents with persistent symptoms after sports-related concussion. Third, the study will also evaluate the impact of the collaborative care intervention on school performance. Finally, we aim to explore the heterogeneity of treatment effects in outcomes by examining the interaction of the treatment effect with group membership in distinct subgroups of the population.

We hypothesize that adolescents who receive the collaborative care intervention will demonstrate clinically and statistically significant reductions in PCS and depressive and anxiety symptoms over the course of the 12-month study compared to the usual care control group. We also hypothesize that adolescents who receive collaborative care will exhibit a clinically meaningful improvement in functioning and health-related quality life compared to the usual care control group. For the third aim, we expect that adolescents who receive the collaborative care intervention will receive individualized treatment and community resource linkages which will improve their school performance and return to full activities at school compared to usual care. Finally, we anticipate that three distinct subgroups will emerge from the study population—adolescents who recover from symptoms, adolescents with chronic psychosocial problems, and adolescents whose symptoms wax and wane over time—and these groups will have heterogeneity in treatment effects.

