#### Power analysis and sample size

Power analyses were conducted using PASS software to determine the appropriate number of participants for the study [91–93]. Based in part on prior investigation by the study team, assumptions including four assessment points (baseline, 3 months, 6 months, and 12 months), equal correlations over time of ρ = 0.7, two-tailed alpha = 0.05, and 10% 12-month attrition were used for all power analyses. We used data derived from our prior large scale collaborative care investigations to estimate symptomatic and quality of life treatment effects for power calculations [25, 94]; data from the pilot were used to corroborate treatment effect estimates derived from these larger scale trials [95, 96]. The study team conservatively estimated that the 12-month persistent concussive symptom treatment effect will be d = 0.35–0.40, using preliminary data derived from prior study team large scale collaborative care investigations [25, 31].

To estimate the power to detect a group-by-time interaction effect on persistent concussive symptoms we used the primary continuous HBI total symptom score with baseline mean = 33.0 and common SD = 11.0. The study will require recruitment of 200 subjects (100 subjects in each group) in order to retain 180 subjects at the 12-month post-injury follow-up. With a final sample of 180 subjects, the power to detect a significant group-by-time interaction with a between-group effect size of d = 0.36 on the HBI somatic symptom scale is 0.80.

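### Three symptom constructs hold equal primary rank with no success rule, while the sample size rests on single tests at two-tailed 0.05

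*Protocol article*

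**What the plan says.** In the protocol article, the heading "Primary outcome measures" covers three constructs of equal rank:

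- **Post-concussive symptoms:** the HBI. "The scale includes youth-report and parent-report versions with established reliability and validity in youth with sports injury".
- **Depression:** the "nine-item Patient Health Questionnaire (PHQ-9) to measure severity of depressive symptoms". Table 1 schedules it as adolescent report, parent report of the youth, and parent self-report.
- **Anxiety:** the GAD-7 and 15 RCADS items. The anxiety section names adolescent report and parent report of the adolescent. Table 1 lists adolescent report and parent self-report only.

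Secondary outcomes start after these, with quality of life: "The Pediatric Quality of Life Inventory (PedsQL) is a 23-item questionnaire".

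Other sections bear on the same question:

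- *Objectives and hypothesis* expects "clinically and statistically significant reductions in PCS and depressive and anxiety symptoms".
- *Data analysis plan and statistical procedures* expects "greater improvement than controls in both self-report and parent report of post-concussive, anxiety, and depressive symptomatic and quality of life outcomes". It also includes quality of life in the primary purpose of the analysis. The effect of interest is one time-by-treatment term per outcome.
- *Power analysis and sample size* says "we used the primary continuous HBI total symptom score", then attaches d = 0.36 and power 0.80 to the HBI somatic scale. Its significance level is "two-tailed alpha = 0.05, and 10% 12-month attrition were used for all power analyses". It also sizes a 12-month HBI responder comparison (44% vs 65%) and the PedsQL. It gives no power for the PHQ-9 or either anxiety scale.

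**The concern.** The sections disagree on what is primary: three constructs in the outcomes section, the HBI alone in the power section, and the three constructs plus quality of life in the analysis section. None says what pattern of results would count as success.

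Two rules are possible, and the design fits neither. If one significant primary result is enough, several chances at 0.05 push the overall error above 5%. If all three constructs must succeed, the error is not inflated, but a power of 0.80 for one HBI test does not describe the chance of success.

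At stake is how a mixed result is read. With benefit on one anxiety scale from one reporter and nothing on the HBI, the text would let one reader call the trial positive and another call it negative. *Dissemination policy* ties a finding of superiority to a further grant application, so the reading has consequences.

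**Working it through.** **Inputs from the article.** Two-tailed alpha 0.05; 180 analysed (90 per arm) of 200 recruited; d = 0.36; correlation over time 0.7; four assessments; stated power 0.80. **Assumption.** The correlation between test statistics of different outcomes is not given. *Background* says only that depressive and other post-concussion symptoms correlate. I use an equal correlation r of 0.3 to 0.7.

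**1. The stated power.** Power = Φ(d/SE − 1.960), with SE = √(2f/90).
- Difference averaged over four assessments: f = (1 + 3×0.7)/4 = 0.775, SE = 0.131, d/SE = 2.743, power 0.783. This is within two points of 0.80.
- Single unadjusted time point: f = 1, SE = 0.149, d/SE = 2.415, power 0.675.
- Change from baseline to 12 months: f = 2×(1 − 0.7) = 0.6, power 0.877.
- 12 months adjusted for baseline: f = 1 − 0.7² = 0.51, power 0.922.
- Linear slope: power 0.90–0.91.

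The 0.80 is therefore reproduced, approximately, as the power of one HBI test at 0.05. The closest formula is a time-averaged difference, although the text calls it a group-by-time interaction.

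**2. Number of symptom tests.**
- 3: one test per construct.
- 5: two reporters for the HBI and PHQ-9, and one youth anxiety test, following Table 1.
- 6: three constructs by two reporters.
- 8: as for 6, but with both anxiety scales tested for both reporters.

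**3. If any one significant result counts.** For k independent tests the error is 1 − 0.95^k: 0.143 (k = 3), 0.226 (5), 0.265 (6), 0.337 (8). For correlated tests, Zᵢ = √r·U + √(1−r)·eᵢ, and the error is P(at least one |Zᵢ| > 1.960).

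| Tests | r = 0.3 | r = 0.5 | r = 0.7 | Favourable direction only, r = 0.3 to 0.7 |
|---|---|---|---|---|
| 3 | 0.14 | 0.13 | 0.11 | 0.07 to 0.05 |
| 5 | 0.21 | 0.18 | 0.15 | 0.11 to 0.07 |
| 6 | 0.24 | 0.21 | 0.16 | 0.12 to 0.08 |
| 8 | 0.30 | 0.25 | 0.19 | 0.15 to 0.10 |

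The nominal values are 0.05 two-sided and 0.025 in the favourable direction.

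**4. If all three constructs must succeed.** Give each test 0.80 power (assumed for depression and anxiety), so that each statistic has mean 1.960 + 0.842 = 2.802. Independent tests give 0.80³ = 0.512. Correlations of 0.3, 0.5 and 0.7 give 0.57, 0.61 and 0.66.

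**5. If all remain primary and alpha is split (Bonferroni).**
- 3 tests: 0.05/3 = 0.0167 each. Power falls from 0.80 to Φ(2.802 − 2.394) = 0.66. Restoring 0.80 needs 180×1.334 = 240 analysed, or 240/0.9 = 267 recruited.
- 6 tests: 0.05/6 = 0.0083 each. Power falls to Φ(2.802 − 2.638) = 0.56. Restoring 0.80 needs 180×1.543 = 278 analysed, or 309 recruited.

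**The case against.** The strongest reply is that the article does not prescribe the inflated procedure. The 0.05 is stated for the power analyses only. Multiplicity control is often left to an analysis plan, and none is shown. The hypotheses are worded jointly, and if every outcome must succeed there is no inflation. The power section already singles out the HBI total as primary.

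Much of this stands. A reader might infer that the trial has a fixed false-positive rate of 18–27%, that each outcome is to be tested at 0.05, and that one win suffices. The documents do not support that. No section states a level for the outcome tests or says that one win is enough. The number of tests ranges from 3 to 8 depending on the section followed, and the correlation is unknown. The two-sided figures also count false harm.

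The reply does not remove the point. The equal primary ranking, the conflicting status of quality of life, and a sample size set on single tests at 0.05 are all stated in this article. A later adjustment could control the error, but at 200 recruited it would cost power (step 5). The joint reading rescues the error rate only by leaving the stated 0.80 no longer describing the hypothesis. Calling the HBI total primary in the power section does not demote depression or anxiety in the outcomes section.

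The absence of a minimum depression or anxiety score at entry has no bearing on the type I error and is not relied on here.

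**Conclusion.** The point holds as an undefined primary family and success rule, not as a proven error rate. If any one result counts and each is tested at 0.05, the only level in the article, the familywise error is about 0.11–0.14 for 3 tests, 0.16–0.24 for 6 and 0.19–0.30 for 8. About half of each is false benefit. If all three constructs must succeed, joint power is about 0.51–0.66.

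The first set of figures rests on assumed correlations of 0.7 to 0.3. The second rests on an assumed 0.80 power for each construct and correlations from 0 to 0.7. Over the ranges shown, either rule departs materially from the 5% error and 0.80 power that the sample size implies. The contradictions between sections on what is primary need no assumption.

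**What to change.** 1. Name one primary outcome: the HBI total score from one stated reporter (for example the adolescent), analysed by the group-by-time model to which the power section refers. The article names no reporter for the sizing, so this is a choice to be made explicitly.
2. Reconcile total and somatic HBI score in *Power analysis and sample size*.
3. Make the PHQ-9, the anxiety scales and the parent reports of the youth secondary, tested in a fixed order or by Holm only after the HBI test succeeds.
4. Treat the PedsQL as secondary in the analysis section too, and keep parents' scores about themselves outside the family.
5. Reconcile Table 1 with the anxiety section on parent report of youth anxiety.
6. State that the 0.80 applies only to the HBI test for which it was calculated. Recompute it if a single 12-month comparison is chosen: at d = 0.36 it would be about 0.68 unadjusted and 0.92 adjusted for baseline.

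Keeping several primary outcomes is possible, but it needs a stated rule and either the power loss or the larger sample in step 5 of the working, or the joint power in step 4.

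The recommended change is wording before database lock, with no added patients or data. It should be made without reference to the interim results planned for February 2019. The downside is that an isolated effect on depression or anxiety could be reported only as secondary.

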### Randomization

Randomization will occur in a 1:1 ratio, in blocks of four to six patients, according to a computer-generated random assignment sequence prepared by the study biostatistician. Once generated, intervention and control group assignments will be entered into a password-protected tracking system with access limited to study coordinator, care manager, and principal investigator. Randomization will be conducted by the study coordinator. After randomization occurs a letter and email will be sent to the referring provider and participant family to notify them as to which group the participant has been randomly assigned.

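### Covariates are chosen by baseline significance tests and by observed dropout, so chance decides the adjustment set; the fix is cheap and the cost to the group-by-time test is small

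*Protocol article*

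**What the plan says.** All of this is in the protocol article under Data analysis plan and statistical procedures, unless another section is named.

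- **Baseline tests.** "Prior to these analyses, we will examine baseline group differences using the appropriate statistics for the distribution of the variable". The stated motive is that "it is essential to control for known confounders in the design and analysis to prevent a biased assessment of the treatment effect". No confounder is named.
- **First rule.** "Baseline injury, demographic, or clinical variables found to be statistically significant in this analysis will also be included as covariates". The analysis referred to is the comparison of the arms at baseline.
- **Second rule.** "We will use statistical logistic models to determine which, if any, demographic or clinical characteristics, including treatment group membership, are predictive of subject attrition". Then: "Any factors observed to explain trends in missing data would be used as covariates in subsequent analyses". No criterion for being predictive is given, and the characteristics are not limited to those measured at baseline.
- **Randomization section.** "Randomization will occur in a 1:1 ratio, in blocks of four to six patients". No stratification factor is given.

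The models are longitudinal, and the effect given priority is the group-by-time interaction. The Power analysis section counts baseline as one of four assessments. Gender, injury type, psychiatric history and trauma history appear by name only in secondary analyses.

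**The concern.** In a randomised comparison a baseline test asks whether allocation produced an imbalance larger than chance. With sound randomisation the answer is known in advance: any significant result is chance. The p-value carries no information on whether the variable predicts outcome, and that is what makes adjustment worthwhile. The first rule therefore adjusts for whatever happens to differ and usually leaves out variables that matter.

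The second rule lets the pattern of dropout change the outcome model. Together they are the only routes by which the article commits to a covariate. At stake are a model that cannot be written down before trial data are examined, possible loss of precision, and possible bias if a variable measured after randomisation came in through the attrition screen.

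**Working it through.** **Inputs from the Power analysis section.** 90 per arm retained, d = 0.36, correlation ρ = 0.7 between visits, two-sided α = 0.05, visits at 0, 3, 6 and 12 months.

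**Assumptions, because the article gives no figure.** Baseline tests at 0.05, independent of each other; covariate-outcome correlation r = 0.3 or 0.5.

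**1. The plan's own power.** For the 3-df group-by-time F test with the difference growing linearly in months to d, the visit pattern is (0, 0.25, 0.5, 1), whose sum of squared deviations is 0.546875. Then λ = 0.36² × 0.546875 / (0.3 × 2/90) = 10.63, and power is 0.786. With equally spaced visits, λ = 10.80 and power is 0.793. The stated value is 0.80, so nothing here rests on a sample-size error.

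**2. Chance of entering the model.** For one variable this equals the test level: 0.05 (or 0.10 if tests were at 0.10). Three given variables are all left out with probability 0.95³ = 0.86. At least one of k tested variables enters with probability 1 − 0.95^k:

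- k = 5: 0.23
- k = 10: 0.40
- k = 20: 0.64

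**3. Type I error.** Simulation with one covariate, a comparison of level, 20,000 runs. Under the rule: 0.046 (r = 0.3) and 0.041 (r = 0.5). Always adjusted: 0.050 and 0.048. For change from baseline the rule and constant adjustment agree: 0.047 each at r = 0.3 and 0.051 each at r = 0.5.

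**4. Power.** Unadjusted anchors come from Φ(d√(n/2)/SD − 1.96), with n = 90 and d√(n/2) = 2.415:

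- 12-month score alone, SD = 1: 0.675
- change from baseline, SD = √(2 × 0.3) = √0.6: 0.877
- 12-month score adjusted for baseline, SD = √(1 − 0.7²) = √0.51: 0.922

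Simulated power (20,000 runs), under the rule against always adjusting:

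| Analysis | r = 0.3 | r = 0.5 |
|---|---|---|
| 12-month score, baseline ignored | 0.673 vs 0.708 | 0.677 vs 0.785 |
| Change from baseline | 0.874 vs 0.873 | 0.872 vs 0.870 |
| Baseline score as covariate | 0.920 vs 0.924 | 0.920 vs 0.933 |

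The losses are 3.5 and 10.8 points in the first row, none in the second, and 0.4 and 1.3 points in the third. A repeat of the first row (10,000 runs) gave 0.678 vs 0.710 and 0.685 vs 0.798, losses of 3.2 and 11.3 points. Allowing for simulation error, the first row is about 3 to 12 points.

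The second row shows no loss because a covariate with the same effect at every visit cancels from a within-person contrast. The third row is small because the baseline score already carries most of the covariate's information. The residual variance is 0.51 without the covariate. With it, the variance is 1 − (ρ² + r² − 2ρr²)/(1 − r²), which is 0.501 at r = 0.3 and 0.480 at r = 0.5. Covariates that change the trajectory over time were not simulated.

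**5. If a post-randomisation variable entered.** As an illustration, suppose the 12-month comparison were adjusted for the 3-month score. The estimate becomes d₁₂ − ρd₃. With an assumed 3-month effect of 0.18 it is 0.36 − 0.7 × 0.18 = 0.23. With 0.36 it is 0.36 − 0.7 × 0.36 = 0.11. This shows what could happen, not what the article plans.

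**The case against.** Four arguments can be made for the plan.

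- **The stated primary effect barely suffers.** This stands. A reader might infer a loss of some 11 power points for the main test. That figure belongs to a 12-month comparison that ignores baseline, whereas the article tests group-by-time in a model that includes it.
- **No false-positive risk is shown.** This also stands. A reader might infer that choosing the model from the data inflates type I error. For the baseline rule the simulated size is at or slightly below nominal. That rule uses allocation and baseline data, not outcomes, so it could be run before outcomes are analysed. The attrition rule does need follow-up data, and the two rules together were not simulated.
- **Other covariates may be intended.** The first rule says such variables will also be included, and known confounders are mentioned, so a list may exist in an analysis plan not shown. That is possible, and the baseline outcome, likely the strongest predictor, is in the longitudinal model as the first assessment. It does not rescue the rule, which the article states outright and which an added list would not cancel.
- **Conditioning on predictors of missingness supports the missing-at-random assumption.** This is a fair reason to use them somewhere. A reader might infer that post-randomisation variables will enter the main model. The article does not say so: it leaves the characteristics unrestricted and notes only that the models permit time-dependent covariates.

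**Conclusion.** The concern holds as a flaw in how covariates are chosen. The article fixes a rule under which chance imbalance and observed dropout determine the adjustment set. A given prognostic variable enters through the baseline tests only about 5% of the time (tests assumed at 0.05), and none is named in advance for the outcome models.

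The statistical cost is modest. Size stays at about 0.04 to 0.05. Power loss is negligible for the group-by-time contrast with a covariate effect constant over time, and about 0 to 1 point with baseline adjustment. It is material, about 3 to 12 points at assumed r of 0.3 to 0.5, only for comparisons of level that make no use of baseline, and possibly for covariates that affect trajectory. Bias through the attrition rule is a possibility left open by the wording, not a stated plan. This is a worthwhile, low-cost improvement; the validity of the trial does not depend on it.

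**What to change.** - Remove significance testing of baseline differences as a way of selecting covariates. Describe the arms at baseline without it.
- Name a short list of baseline prognostic covariates and use it whatever the balance: for example age, sex, time since injury, prior concussion and prior psychiatric history. Keep the baseline outcome in the longitudinal model as now. If a covariate is expected to affect the trajectory, state in advance whether its interaction with time is included.
- Restrict predictors of attrition to baseline variables. Use those not on the list in the missing-data sensitivity analyses, or as auxiliary variables in imputation, and not as additions to the main model.
- Record the list before any outcome is analysed by arm.

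The suggested variables are already covered by the Eligibility criteria, Baseline measures and History of sports concussion sections or by the planned secondary analyses, so no new data are needed. The cost is a change of wording and a few degrees of freedom.
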